# Efficacy and Safety of Inhaled Ciclesonide in Treating Patients With Asymptomatic or Mild COVID-19 in the RACCO Trial: Protocol for a Multicenter, Open-label, Randomized Controlled Trial

**DOI:** 10.2196/23830

**Published:** 2020-12-31

**Keywords:** COVID-19, SARS-CoV-2, proposed therapy, therapy, drug, treatment, protocol, randomized controlled trial, intervention

## Abstract

**Background:**

Currently, there are no specific effective treatments for SARS-CoV-2 infection; however, various COVID-19 treatment options are under investigation. It is vital to continue investigating the landscape of SARS-CoV-2–induced pneumonia and therapeutic interventions.

**Objective:**

This paper presents the protocol for a randomized controlled trial that aims to compare the pneumonia exacerbation rate between ciclesonide (ALVESCO; Teijin Pharma Limited) administration and symptomatic treatment in patients with COVID-19 and to determine the efficacy of ciclesonide. The secondary objectives are to investigate the safety of ciclesonide administration, changes in clinical and laboratory findings, and the number of viral genome copies of SARS-CoV-2 over time between the 2 groups.

**Methods:**

In this investigator-initiated, exploratory, prospective, multicenter, parallel-group, open-label, randomized controlled trial, a total of 90 patients diagnosed with COVID-19 will be recruited from 21 hospitals in Japan based on specific inclusion and exclusion criteria. Participants will be randomized either to the ciclesonide group, which will receive a 400-µg dose of ciclesonide 3 times per day over a 7-day period, or to the symptomatic treatment group. Both groups will receive antitussives and antipyretics as required. Data collection for various parameters will be conducted on days 1, 2, 4, 8, 22, and 29 to record baseline assessments and the findings over an extended period. Computed tomography images taken prior to drug administration and 1 week following treatment will be compared, and efficacy will be confirmed by checking for pneumonia exacerbation. Primary endpoint analysis will be performed using the Fisher exact test to determine statistically significant differences in the pneumonia exacerbation rate between the ciclesonide and symptomatic treatment groups.

**Results:**

The first trial participant was enrolled on April 3, 2020. Recruitment is expected to be completed on September 30, 2020, while follow-up assessments of all participants are expected to be completed by October 31, 2020. The study results will be published in a peer-reviewed scientific journal.

**Conclusions:**

The RACCO (Randomized Ciclesonid COVID-19) study will provide definitive comparative effectiveness data and important clinical outcomes data between the ciclesonide and symptomatic treatment groups. If the hypotheses that pneumonia exacerbation rate reduction is more significant in the ciclesonide treatment group than in the symptomatic treatment group and that ciclesonide is safe for use are valid, ciclesonide will serve as an important therapeutic option for patients with COVID-19.

**Trial Registration:**

Japan Registry of Clinical Trials jRCTs031190269; https://jrct.niph.go.jp/en-latest-detail/jRCTs031190269

**International Registered Report Identifier (IRRID):**

DERR1-10.2196/23830

## Introduction

### Background and Rationale

An outbreak of severe respiratory illness occurred in Wuhan, China at the end of December 2019. The World Health Organization and China were alerted by an increase in the number of patients with pneumonia of unknown etiology. In January 2020, it was reported that a novel type of coronavirus, SARS-CoV-2, was responsible for the outbreak [1]. Three months later, almost half a million cases of this contagious infection had been identified across 197 countries [2], and on March 11, 2020, the World Health Organization declared the COVID-19 outbreak as a pandemic [3].

While most COVID-19 cases result in mild symptoms, some cases progress to pneumonia, acute respiratory distress syndrome, and death [4,5]. The case fatality rate reported across various countries, settings, and age groups is highly variable, but ranges from less than 1% to 19% [6]. Among hospitalized patients, the case fatality rate has been reported to be greater than 10% in some centers [7].

There is currently no specific effective treatment for SARS-CoV-2 infection, but various options and strategies for treating COVID-19 are under investigation worldwide [8]. Lu et al [9] reported that antiviral molecules, nucleoside analogs, neuraminidase inhibitors, therapeutic peptides, RNA synthesis inhibitors, anti-inflammatory drugs, and Chinese traditional medicine could be therapeutic options for SARS-CoV-2 infection. Currently, the standard treatment methods for clinicians only involve symptomatic treatment; therefore, it is vital to continue investigating the landscape of SARS-CoV-2–induced pneumonia and therapeutic interventions. The asthma drug ciclesonide (ALVESCO) is a pressurized metered-dose inhaler that uses the glucocorticoid ciclesonide and originates from Nycomed. It is now developed, manufactured, and marketed by numerous pharma companies worldwide, including Covis Pharma, Takeda, Sunovion Pharmaceutical, and Teijin Pharma [10]. Teijin Pharma in Japan developed ciclesonide for adult bronchial asthma in April 2007, and it was approved for child doses in January 2011. This drug acts by reducing the swelling of the airways in the lungs in order to make breathing easier. After the oral inhalation of ciclesonide, a prodrug is enzymatically hydrolyzed in the lungs to an active metabolite (ie, des-ciclesonide). Des-ciclesonide has an anti-inflammatory effect and binds to glucocorticoid receptors, thereby controlling chronic inflammation in the air ducts [11].

Preclinical data [12] have suggested that ciclesonide could potentially treat COVID-19, since it has been shown to suppress the replication of human coronaviruses (eg, Middle East respiratory syndrome–related coronavirus) in cell cultures [13] and exhibit strong antiviral activity, even against SARS-CoV-2 [12]. Additionally, a recently published case series [14,15] showed that treatment with this drug has led to favorable outcomes in 3 patients with confirmed COVID-19 [14,15]. These case reports from Iwabuchi et al [14,15] indicated that the ideal administration period should be in the early intermediate stage of infection or in the initial stage of pneumonia, prior to the worsening of symptoms. Covis Pharma has launched a phase III clinical trial in the United States to evaluate its asthma drug, ciclesonide (ALVESCO), for its ability to treat nonhospitalized, symptomatic patients with COVID-19 aged ≥12 years. As of May 22, 2020, the drug is currently being investigated for the treatment of COVID-19 in several countries, such as Australia, South Korea, Sweden, the United Kingdom, and the United States [10], and the results are not yet available.

More studies on ciclesonide are required to assess its efficacy and safety in treating patients with COVID-19. This prospective randomized controlled trial in Japan aims to investigate the efficacy and safety of ciclesonide in treating patients with COVID-19 during the early stages of SARS-CoV-2 infection. The accumulation of findings from this study will be significant for the treatment of COVID-19.

### Objectives

The primary objective of the RACCO (Randomized Ciclesonide COVID-19) trial is to compare the pneumonia exacerbation rate between the ciclesonide and symptomatic treatment groups, which consist of patients with COVID-19, and to determine the efficacy of ciclesonide. The secondary objective is to investigate the safety of ciclesonide administration by comparing the rate of adverse events between both groups. In addition, changes in clinical and laboratory findings and changes in the number of copies of the viral genome over time will be monitored between the 2 treatment groups.

### Trial Design

This is an investigator-initiated, exploratory, prospective, multicenter, parallel-group, open-label, randomized controlled trial. Figure 1 describes and outlines the design in more detail. The first trial participant was enrolled on April 3, 2020. Recruitment is expected to be completed on September 30, 2020, while the follow-up of all participants is expected to be completed by October 31, 2020.

**Figure 1 figure1:**
[figure not shown]
Trial design and outline.

## Methods

### Ethical Approval

This study is being conducted in compliance with the Declaration of Helsinki 2013; Clinical Trials Act; Clinical Trials Act Enforcement Regulations; 2018 Ordinance of the Japanese Ministry of Health, Labor, and Welfare; and Japanese Good Clinical Practice (GCP). In the Japanese GCP, principal investigators in all participating institutions serve as the study sponsor for investigator-initiated, registration-directed trials, and hospital directors take responsibility for the study conduct. Prior ethical approval for the protocol and the informed consent document was obtained from The University of Tokyo, Clinical Research Review Board (Approval No CRB3180024), and each participating hospital investigator received permission from the administrator to conduct the study, after which the representative physician submitted the explanatory and consent documents to the Ministry of Health, Labor, and Welfare in Japan. This trial is registered and recorded in the Japan Registry of Clinical Trials (jRCT; jRCTs031190269), and research only commenced after the jRCT release.

### Study Setting

The main study site is the Center Hospital of the National Center for Global Health and Medicine, Tokyo, Japan, but several other hospitals are participating in this trial. A total of 90 patients diagnosed with COVID-19 were recruited from 22 hospitals in Japan. Textbox 1 lists the medical institutions participating in this trial.

The sample size for the RACCO trial (N=90) is based on a statistical minimum number of patients required for each treatment arm, to control for pneumonia onset and the final number of patients who will undergo the full analysis and complete the study. The sample size calculation is outlined under the Statistical Methods section.

Participating medical institutions.

### Recruitment

Strategies have been implemented to ensure maximum enrollment at each site. Each study site has a target number of patients to enroll. Furthermore, our study period includes the following: the registration period, which lasts from March 30 to September 30, 2020; the observation period, which lasts from March 30 to October 31, 2020; and the implementation period, which lasts from March 30 to October 31, 2021.

### Eligibility Criteria

Our inclusion criteria for study participants are as follows: (1) provided written consent for research participation; (2) aged ≥20 years at the time of consent acquisition, regardless of sex; (3) tested positive for SARS-CoV-2 based on polymerase chain reaction (PCR) results or the loop-mediated isothermal amplification method (4) had no clear indications of COVID-19–induced pneumonia on simple chest images; (5) hospitalized during the trial drug administration period (ie, 1 week); and (6) had the ability to receive ciclesonide inhalation using an inhalation-assisting device.

Our exclusion criteria for study participants are as follows: (1) a medical history of ciclesonide hypersensitivity; (2) the presence of an infectious disease or deep-seated mycosis other than COVID-19, for which there is no effective antibacterial agent; (3) the presence of chronic respiratory diseases, such as chronic bronchitis; (4) current treatment with inhaled or oral steroids; (5) a history of a continuous fever of ≥37.5°C that lasted for over 7 days; (6) current treatment with agents that have potential therapeutic effects against COVID-19 and may affect the efficacy assessments, including remdesivir, lopinavir/ritonavir compound drugs, favipiravir, interferon, and hydroxychloroquine; and (7) conditions deemed unsuitable for research by the principal physician or subphysician.

### Informed Consent

Physicians trained in GCP will determine participants’ eligibility, discuss the trial with the patients, and seek their informed consent. Explanatory and consent documents approved by the authorizing clinical study examination committee and authorized by the Minister of Health, Labor, and Welfare will be provided to the research participants, and sufficient written and verbal explanations will be provided in order to avoid forceful or unfair influences. Consent from research participants will be obtained by having them sign and date the consent document.

### Patient Registration and Allocation Method

After obtaining written consent from the research participants, the principal physician or subphysician will confirm whether a research participant is suitable for the trial by verifying the inclusion and exclusion criteria, promptly performing electronic data capture (EDC)-based patient registration, and acquiring the allocation results.

A stratified block randomization method will be used to allocate participants into 2 groups, the ciclesonide group and symptomatic treatment group. Allocation adjustment factors include the numbers allocated to each facility, fever temperature (ie, over or below 37.5°C), and age (ie, over or under 60 years). Allocation results will be displayed on the EDC system after inputting and confirming the allocation adjustment factors into the EDC system.

The principal physician or subphysician will commence research treatment in accordance with the allocation results. Research participants will be issued a research ID that is specific to the proposed research.

### Interventions

Participants will be randomized to 1 of the 2 treatment groups. In the ciclesonide group, a 400-µg dose of ALVESCO, which is manufactured by Teijin Pharma Limited, Japan, will be administered to patients with asymptomatic or mild COVID-19 3 times per day over a continuous 7-day period. The patients will also receive antitussives and antipyretics as needed. In the symptomatic treatment group, only antitussives and antipyretics will be administered to the patients as needed.

Ciclesonide has not been approved for COVID-19 treatment in Japan or internationally, and is used only for research purposes.

### Criteria for the Discontinuation of Treatment/Intervention

The representative physician will review the continuation of research implementation when the following events occur: (1) when important information relating to the trial drug quality, efficacy, and safety; factors that may affect the research implementation or continuation; and other factors that affect the effective implementation of the research is obtained; (2) when research subject incorporation and the attainment of the predicted number of participants becomes difficult; (3) when research objectives are achieved during intermediate analysis prior to reaching the predicted number of participants or completion of the predicted period; (4) when the authorizing clinical study examination committee instructs a revision of the research proposal and when this revision is difficult to incorporate; (5) when the authorizing clinical study examination committee issues a suspension; and (6) when serious or continuous violations of the clinical research methods, enforcement regulations, or this research proposal are noted.

### Strategies to Improve Adherence to Intervention

A face-to-face initiation meeting was held prior to the commencement of the trial at each site. Site investigators and research staff engaged with their multidisciplinary teams and provided training.

The principal physician or subphysician will provide guidance for research participants prior to the start of research. Research participants will be shown an inhalation guidance video beforehand and will be guided on how to use the AeroChamber Plus (Trudell Medical UK Limited) in order to increase respiratory efficiency. Furthermore, an asthma diary will be distributed to the patients in advance. Patients are to confirm that the inhalant has not yet been administered, and the patient will be instructed to check the confirmation column after inhalation.

### Relevant Concomitant Care Permitted or Prohibited During the Trial

The following drugs are prohibited during the research implementation period (ie, from consent acquisition to the final observation date): (1) orally or intravenously administered systemic adrenocortical steroids, (2) inhaled steroids other than inhaled ciclesonide, and (3) drugs that may have therapeutic effects against COVID-19 (eg, remdesivir, lopinavir/ritonavir compound drugs, favipiravir, interferon, and hydroxychloroquine).

### Provisions of Posttrial Care

The expected research participation period will last for approximately 1 month, after consent acquisition (ie, 1 week for the protocol treatment period and 3 weeks for the follow-up period). Research participants will be hospitalized during the treatment period, and outpatient follow-up observations will be permitted following the end of the protocol treatment period. In cases where the research participants experience adverse events linked to the treatment, follow-up examinations are to be conducted until the principal physician or subphysician has ensured the safety of the research subject.

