**Figure 2 figure2:**
[figure not shown]
Participant timeline, enrollment, interventions, and assessments.

**Table 1 table1:** Assessment details and days of implementation.

Assessment	Screening period	Administration period	Observation period	Suspension
Hematologic test^a^	Day 1	Days 4 and 8	Day 15: implemented as an outpatient examination when the research subject has been discharged. Days 22 and 29: unnecessary when the research subject has been discharged.	Unnecessary when the research subject has been discharged
Biochemical blood inspection^b^	Day 1	Days 4 and 8	Day 15: implemented as an outpatient examination when the research subject has been discharged. Days 22 and 29: unnecessary when the research subject has been discharged.	Unnecessary when the research subject has been discharged
Infectious disease inspection^c^	Day 1	Not implemented	Not implemented	Not implemented
Coagulation test^d^	Day 1	Days 4 and 8	Day 15: implemented as an outpatient examination when the research subject has been discharged. Days 22 and 29: unnecessary when the research subject has been discharged.	Unnecessary when the research subject has been discharged
Coronavirus inspection^e^	Day 1	Day 8	Day 15: implemented as an outpatient examination when the research subject has been discharged.	Implemented when suspended before Day 8
Image inspection^f^	Day 1	Day 8	Day 15 Days 22 and 29: unnecessary when the research subject has been discharged.	Implemented when suspended before Day 8
Peak flow measurement^g^	Day 1	Performed daily	Days 15, 22, and 29	Not implemented
Questionnaire^h^	Day 1	Subjective symptoms recorded daily	Day 15: implemented as an outpatient examination when the research subject has been discharged. Days 22 and 19: obtained by phone when the research subject has been discharged.	Obtained by phone when the research subject has been discharged
Comprehensive assessment by the physician	Day 1	Day 8	Day 15: implemented as an outpatient examination when the research subject has been discharged. Days 22 and 29: unnecessary when the research subject has been discharged.	Unnecessary when the research subject has been discharged
Confirmation of combined drug usage conditions^i^	Not implemented	Information on the presence of concomitant medications collected daily	Days 15, 22, and 29	Not implemented

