^a^Leukocyte count, neutrophil count, lymphocyte count, hematocrit level, hemoglobin level, platelet count, and blood sedimentation are to be measured for the hematologic tests.

^b^Albumin, bilirubin, aspartate transaminase, alanine transaminase, lactate dehydrogenase, γ-glutamyl transpeptidase, alkaline phosphatase, creatinine kinase, creatinine, blood urea nitrogen, sodium, potassium, C-reactive protein, glutamic acid, and procalcitonin levels are to be measured for biochemical blood inspections.

^c^Hepatitis B surface antigens, hepatitis B core antibodies, hepatitis C virus antibodies, and HIV antibodies are to be measured for infectious disease inspections.

^d^Prothrombin time, activated partial thromboplastin time, fibrinogen level, and D-dimer level are to be measured for coagulation tests.

^e^For coronavirus inspections, SARS-CoV-2 real-time polymerase chain reaction samples are to be collected with nasal swabs and measured on the day of and 8 days after hospitalization, and serum SARS-CoV-2 antibodies are to be measured on the day of and 8 days after hospitalization.

^f^Chest computed tomography scans are to be taken on the day of and 8 days after hospitalization, and simple chest radiographs are to be taken 4, 8, 15, 22, and 29 days after hospitalization. In addition, image inspections will be conducted as necessary when symptom exacerbation is suspected. Simple chest radiographs on days 22 and 29 will not be taken if the research subject is already discharged. Computed tomography is to be performed when pneumonia worsens within 8 days of hospitalization and when the research is suspended.

^g^Peak expiratory flow is to be measured every morning with a peak flow meter during hospitalization and recorded in a diary.

^h^To be conducted prior to assessment by the physician (eg, before the examination).

^i^Information on drug and treatments other than the trial drug are to be collected.

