### Adverse Event Reporting

The incidence of adverse events, including abnormal variations in clinical inspection values and physiological function inspections, will be recorded. Adverse event incidence duration/elimination duration, extent, treatment, outcomes, severity assessments, correlation with medicinal drugs, and predictability are to be recorded in the diagnostic record and case report.

Adverse event extent will be determined based on certain criteria. Mild adverse events refer to conditions in which continued drug administration is possible with no treatment. Moderate adverse events refer to conditions in which continued drug administration is possible with some form of treatment. Severe adverse events refer to conditions in which drug administration is or should be suspended.

Adverse event severity will be determined using the following criteria: (1) death, (2) conditions that may lead to death, (3) conditions for which hospitalization at a medical institution is necessary or hospitalization duration must be extended for treatment (4) disorders, (5) conditions that may lead to disorders, (6) conditions that are severe according to criteria 1-5, and (7) congenital illnesses or abnormalities due to prior generations. All conditions that are not considered severe will be categorized as nonsevere.

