#### Safety Analysis

The safety endpoints include adverse event incidence and rates. The 95% confidence intervals for determining binomial distribution accuracy will be calculated for the estimated rates that relate to the incidence number and presence of adverse events. Intergroup comparisons will be conducted using the Pearson Chi-squared test or Fisher exact test. The significance level of hypothesis testing will be set at 5% for both sides.

Recorded metrics that are calculated for continuous data, such as clinical inspection criteria and vital signs, and suitable methods (eg, number and percentage) will be used as categorical variables for each group.

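### The adverse event comparison has no stated window, yet on days 22 and 29 only inpatients have tests whose abnormal results count as events; if stay differs by arm, test-detected events are under-counted in the arm discharged sooner

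*Protocol article*

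**What the plan says.** The secondary objective in the protocol article (Objectives) is to "investigate the safety of ciclesonide administration by comparing the rate of adverse events between both groups". For adverse event incidence, the Safety Analysis section says "Intergroup comparisons will be conducted using the Pearson Chi-squared test or Fisher exact test", at the two-sided 5% level. Analysis Sets puts all participants in the safety set. No time window for the comparison is given. The nearest thing to one is the participation period under Provisions of Posttrial Care: "The expected research participation period will last for approximately 1 month, after consent acquisition".

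Adverse Event Reporting makes test results a source of events: "The incidence of adverse events, including abnormal variations in clinical inspection values and physiological function inspections, will be recorded".

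Table 1 schedules haematology, biochemistry and coagulation tests on days 4 and 8, and on day 15 for everyone, as an outpatient visit for those already discharged. For the later visits, the rows for these tests say "Days 22 and 29: unnecessary when the research subject has been discharged". The imaging footnote agrees: "Simple chest radiographs on days 22 and 29 will not be taken if the research subject is already discharged". What remains for discharged patients is mainly the questionnaire: "Days 22 and 19: obtained by phone when the research subject has been discharged" (the 19 is evidently a slip for 29). Outpatient follow-up is allowed from the end of the treatment week: "outpatient follow-up observations will be permitted following the end of the protocol treatment period".

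The Hospital Discharge section compares discharge between arms as an outcome, and the trial is open-label.

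**The concern.** A scheduled test can create a countable adverse event, and on days 22 and 29 whether the test is done depends on whether the patient is still in hospital. Discharge happens after randomization and may be affected by treatment. So the chance that an abnormality is found, and not only the chance that it occurs, can differ by arm. A patient who was not tested is not recorded as missing in an any-event proportion. That patient counts as event-free.

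If ciclesonide shortens stay, its patients have fewer chances to show an abnormal value, and some real harm could be hidden. If it lengthens stay, it could look worse than it is. The Abstract and Discussion both make the drug's usefulness depend on its being safe for use, and this comparison is the main evidence for that.

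**Working it through.** The article gives no figure for the safety comparison, so there is none to reproduce. Its one design figure, 84 patients for 35% versus 10%, belongs to the primary endpoint and has no bearing here.

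**Inputs from the article.** Post-baseline bloods on days 4, 8 and 15 for all patients, and on days 22 and 29 for inpatients only (Table 1). 45 patients per arm (Sample Size). Fisher's exact test at a two-sided 5% level (Safety Analysis).

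**Assumed inputs, because the article gives none.** *h* is the risk of a new test abnormality at each visit, the same in both arms: 0.05, 0.10 or 0.20. *d* is the share discharged before day 22.

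**Model.** Discharged patients have three test rounds and the others five:

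P(at least one test-detected event) = d[1 − (1 − h)³] + (1 − d)[1 − (1 − h)⁵]

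For h = 0.10 the two brackets are 1 − 0.9³ = 0.271 and 1 − 0.9⁵ = 0.410.
- d = 0.9: 0.9 × 0.271 + 0.1 × 0.410 = 0.285
- d = 0.5: 0.5 × 0.271 + 0.5 × 0.410 = 0.340

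Results for 90% versus 50% discharged before day 22, with no true difference between arms:

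| h | Sooner-discharged arm | Later-discharged arm | Gap (points) | Risk ratio |
|---|---|---|---|---|
| 0.05 | 15.1% | 18.4% | 3.3 | 0.82 |
| 0.10 | 28.5% | 34.0% | 5.5 | 0.84 |
| 0.20 | 50.6% | 58.0% | 7.4 | 0.87 |

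On 45 patients per arm, 3.3 to 7.4 points is 0.033 × 45 = 1.5 to 0.074 × 45 = 3.3 patients. With smaller differences in discharge the risk ratio is nearer 1: 0.90 to 0.93 for 90% versus 70%, and 0.91 to 0.94 for 70% versus 50%. With equal *d* it is exactly 1.

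**Effect on the test.** With 45 per arm, the rejection rate of Fisher's test at 5% is about 2.6% to 3.1% without the distortion. It is at most 6.8% across these scenarios.

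**Sensitivity to what is found after discharge.** A second model takes any adverse event, with a common 30% rate to day 15, and lets *q* be the chance that each late inpatient round finds a first event. With h22 and h29 the shares in hospital on those days, and nothing found after discharge:

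P = 1 − 0.7[h29(1 − q)² + (h22 − h29)(1 − q) + (1 − h22)]

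- Milder case: q = 0.15; (h22, h29) = (0.4, 0.2) for control and (0.2, 0.1) for ciclesonide. Control 1 − 0.7 × 0.9145 = 36.0%; ciclesonide 1 − 0.7 × 0.95725 = 33.0%. Gap 3.0 points.
- Stronger case: q = 0.30; (0.5, 0.3) and (0.2, 0.1). Control 1 − 0.7 × 0.787 = 44.9%; ciclesonide 1 − 0.7 × 0.919 = 35.7%. Gap 9.2 points.

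If discharged patients' events are instead found at half the inpatient rate (q/2 per round):
- Milder case: 1 − 0.7 × 0.8151 = 42.9% versus 1 − 0.7 × 0.8354 = 41.5%. Gap 1.4 points.
- Stronger case: 1 − 0.7 × 0.6273 = 56.1% versus 1 − 0.7 × 0.6865 = 51.9%. Gap 4.1 points from unrounded values.

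**After the fix.** Counting test-detected events only to day 15 gives 14.3%, 27.1% and 48.8% in both arms for h = 0.05, 0.10 and 0.20, so the risk ratio is 1.00 when true risk is equal.

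**The case against.** The strongest reply is that the Safety Analysis section states no window, and an analysis plan that is not shown may set one. A reader might infer that the protocol compares adverse events over the whole month. It does not say so. One month is the length of participation, and the concern therefore has to be put conditionally. What stands is that the article itself fixes the test, the event definition and a discharge-dependent schedule. Applied together without a cut-off, they give unequal detection whenever stay is unequal.

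A reader might also infer that the arm discharged sooner will look safer, by up to 9 points. The documents do not support this either. They give no event or discharge rates, the direction depends on which arm leaves hospital first, and the 9 points require that nothing is found after discharge although a phone questionnaire is scheduled. The models also treat staying in hospital as unrelated to having had an event by day 15. Long-stay patients may well have had one already, in which case a later abnormality would not change an any-event proportion. More events in the longer-stay arm may also be genuine, since the article counts prolonged hospitalization for treatment among its severity criteria.

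Surveillance after discharge is not nil. Concomitant drugs are listed for days 15, 22 and 29 with no discharge exception. So is peak flow, although its footnote ties it to hospitalization. Follow-up examinations continue for treatment-linked events, but that does not help find new ones. The late physician assessment cannot carry the argument: Table 1 lists it for inpatients on days 22 and 29, while Data Collection Items and Management lists it on days 8 and 15 relative to day 1. Bloods, coagulation tests and radiographs suffice without it.

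**Conclusion.** The point holds in a limited form. If test-detected adverse events are counted over the whole participation period and length of stay differs by arm, they are under-counted in the arm discharged sooner. The treatment week and the week after it are covered by the same scheduled bloods in both arms, so only the day 22 and 29 rounds are affected.

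The bias is zero if stay is equal and probably modest otherwise: about 3 to 7 points for test-detected events with a 40-point difference in discharge, and less with smaller differences. Those figures rest on assumed visit risks and discharge shares, and the true size cannot be derived from the article. The main risk is a distorted safety estimate rather than a false significant result.

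It would go too far to conclude that every event after day 15 is unusable. Symptomatic and serious events depend much less on scheduled tests and can still be reported after discharge.

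**What to change.** In Safety Analysis:
- Limit laboratory- and radiograph-detected adverse events in the between-arm test to those found up to day 15, the last visit that Table 1 schedules regardless of discharge.
- Report test abnormalities from days 22 and 29 descriptively by arm, with the number of patients still in hospital on each day.
- Keep symptomatic and serious adverse events compared over the full follow-up.
- Add a comparison of all events to day 15 as a sensitivity analysis.

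Separately, reconcile Table 1 with Data Collection Items and Management on whether the physician assessment takes place on days 22 and 29.

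No visit or test changes. The cost is that late test abnormalities leave the formal test, though they are still reported, and that each event must be classed as test-detected or symptomatic, preferably without knowledge of arm. The change equalizes scheduled testing only. Patients discharged between the end of treatment and day 15 are still observed less closely between visits than those on the ward.
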